#### Measures of harm

A serious adverse event is defined as an event that: (1) results in the participant’s death, (2) is a suicide attempt; (3) results in hospitalization for non-suicidal self-harm; or (4) results in hospitalization for mental health problems. Clinicians are instructed to report serious adverse events at any stage during therapy within one working day of being aware of the event. A report of a serious adverse event is followed by a telephone call to the clinician from the research team to collect additional information on the serious adverse event, in order to determine the relationship to the study, and the appropriate course of action (continuation or withdrawal from the trial). All serious adverse events are reviewed by a senior clinician independent of the study and reported to the independent data monitoring committee (from the Health Research Council) and the trial steering committee.

Moderate adverse events are defined as: (1) hospitalization for any medical reason, other than mental health problems; (2) serious behavioral problem (i.e., suspension or expulsion from school, running away from home, or problems with the police); or, (3) the use of formal respite care. Information on moderate adverse events is recorded when reported during the study and also collected from the parents at follow-up interview. These events are also reported to the independent data monitoring committee (from the Health Research Council) and the trial steering committee.

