### Exclusion criteria

Participants are ineligible if:They are currently receiving other psychosocial treatment for their disorder within or outside CAMHS;They have a primary disorder of psychosis, intellectual disability, attention deficit-hyperactivity disorder (where the primary reason for referral is inattention or over-activity), autism, or an eating disorder;They are acutely suicidal; or,They have a sibling who has previously been recruited into the study.

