One of the practical challenges for this study is determining the end of treatment because services have different guidelines in place regarding discharge (e.g., a case can be left open for a number of weeks after a proposed final session, in case a youth and their family would like an extra ‘top-up’ session). If needed, the regular weekly assessments and the therapy log data will allow us to determine retrospectively when treatment ended and link this to the correct weekly telephone administered assessments. Another issue has been the recruitment of youths at Māori and Pacific sites. The challenges that impacted on recruitment of these groups included the smaller pool of clinicians at Kaupapa Māori and Pacific services, the smaller proportion of youths meeting study criteria because of high acuity of the problems (including suicidality) and the lower numbers of youths within our age range.

This is a pragmatic trial [41] and accordingly the exclusion criteria have been kept to a minimum and youth participants’ presentation (not their diagnoses) have determined eligibility for participation in the study. As such, we believe this study will have good external validity, because the participants reflect the heterogeneity of youth from ‘real-life’ clinical services. Hence the findings will be applicable to other CAMHS in New Zealand and will probably be of relevance to other countries that have a comparable healthcare workforce and service delivery models.

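### Apart from suicide attempts, the adverse event definitions count self-harm and suicidality as such only after hospitalization or death, so lesser but important episodes are neither serious nor moderate events

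*Protocol article*

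**What the plan says.** All wording is from the protocol article. Under Measures of harm, the first two serious criteria carry no admission condition: "1) results in the participant’s death, (2) is a suicide attempt". The other two require one: "3) results in hospitalization for non-suicidal self-harm; or (4) results in hospitalization for mental health problems".

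The same section defines moderate events by three items: "1) hospitalization for any medical reason, other than mental health problems"; a serious behavioral problem, limited to "i.e., suspension or expulsion from school, running away from home, or problems with the police"; and "3) the use of formal respite care".

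The secondary outcomes include the number and types of events in these two classes. Clinicians report serious events during therapy. Moderate events are recorded when they come to light and are also asked about in the parent interview at three months, which Table 1 assigns to the research assistant. Both classes go to the independent data monitoring committee and the trial steering committee. Collection of moderate events was added during the trial at that monitoring committee's request (Changes to design during the trial).

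Suicidality appears in two other places. The exclusion criteria bar youths if "They are acutely suicidal". The Discussion, explaining slow recruitment at Māori and Pacific sites, mentions "high acuity of the problems (including suicidality".

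**The concern.** The trial enrols 7 to 14 year olds with anxiety, depression, trauma-related symptoms or disruptive behavior. Self-harm is recognized as a harm in the serious definition, but only above the admission threshold (suicide attempts and deaths apart). One would expect a moderate class, which sits below serious, to take in the episodes that fall short of that threshold. It does not. Read literally, a school suspension is an adverse event that goes to the monitoring committee, while repeated self-harm managed without admission is not an event of either class.

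At stake is what the harm outcome and the committee can show. If one arm had more self-harm or suicidality below the admission threshold, the planned event counts need not reveal it.

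**Working it through.** The document gives no figure on this point, so there is none to reproduce. The check is to apply each criterion to each kind of episode.

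| Episode | Serious list | Moderate list | Result |
|---|---|---|---|
| Suicide attempt, not admitted | Yes, criterion 2 | – | Counted |
| Non-suicidal self-harm, admitted | Yes, criterion 3 | – | Counted |
| Suicidality leading to a mental health admission | Yes, criterion 4 | – | Counted |
| Non-suicidal self-harm, not admitted | No | No | Not counted as such |
| New acute suicidality, no attempt, not admitted | No | No | Not counted as such |
| School suspension | No | Yes, item 2 | Counted |

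The gap is thus rows four and five, and no more.

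**Could the moderate list be read more widely?** Item 1 needs a hospitalization, and one that is not for mental health. Item 2 is introduced by *i.e.*, which closes the list at school exclusion, running away and police involvement. Item 3 is respite care. An episode of self-harm or suicidality that also led to one of these would be counted, but under that heading.

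**Is there another record?** Table 1 has two adverse event rows, one for each class. The harm outcome consists of those two classes. The article describes the Brief Problem Monitor, Strengths and Difficulties Questionnaire, Child Health Utility and Development and Well-Being Assessment as measures of problems, quality of life or diagnosis. It presents none of them as a record of self-harm, or as something sent to the committee. As described, the scheduled harm enquiry to parents at three months covers moderate events only, so it has no self-harm item.

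**Is this detail left to a fuller document?** No. Both classes are stated as definitions and enumerated. The weakness lies in what the article fixes, not in what it leaves out.

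**The case against.** The strongest reply is that the threshold is a reasonable trade-off. Attempts and admissions are hard events. Episodes below admission are softer and more open to unequal detection: MATCH-ADTC clinicians review each youth in weekly expert supervision and see weekly eMonitor summaries, while usual-care clinicians have no eMonitor access. Counting spontaneous reports by arm could make MATCH-ADTC look more harmful because it is watched more closely. This stands, and it shapes the fix. It does not justify having no record, because the parent interview is done by a research assistant blind to allocation.

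It is also fair to say that an entry exclusion need not be mirrored as an event category, and that the Discussion's remark on suicidality concerns recruitment rather than risk during the trial. The point therefore rests mainly on the two lists themselves.

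Four stronger readings are tempting, and the document does not support them.

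- *All self-harm without admission is missed.* Any suicide attempt is serious, admitted or not.
- *The trial is blind to these episodes, so an arm with more of them would be declared equally safe.* Some would surface through respite care, police contact, running away or suspension. The article describes no between-arm test of harms. A difference could go unreported; it is not certain to.
- *Dependence on admission biases the comparison.* Clinicians were randomized within service or team, and both arms have the support of their team leaders and clinical managers, so differences in admission practice between sites are largely balanced. The influence of individual clinicians remains possible but is not shown.
- *The loss can be put as power.* With 100 per arm and two-sided 0.05, power is about Φ(d/SE − 1.96), where SE = √[(p₁(1−p₁) + p₂(1−p₂))/100]. Assuming 2% v 4%, d/SE = 0.02/√0.00058 = 0.83 and power is about 13%. Assuming 15% v 30%, d/SE = 0.15/√0.003375 = 2.58 and power is about 73%. The rates are freely chosen and the test is not planned. The contrast shows only that commoner events give more power.

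**Conclusion.** The point holds in a limited form. Two kinds of episode fall outside both definitions: non-suicidal self-harm without hospitalization, and new acute suicidality without an attempt or admission. The secondary harm outcome and the committee reports do not record them as such.

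No numerical impact can be given, since the document states no event rates. The three primary outcomes are untouched, and the document does not contradict itself here. The conclusion assumes that the two lists are applied as written and that no further harm record exists beyond those the article lists. It is worth correcting because the remedy is small and the moderate class was itself added mid-trial.

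**What to change.** Add a fourth item to the moderate adverse event definition: *non-suicidal self-harm, or new acute suicidality, not resulting in a suicide attempt or hospitalization*. The qualifiers keep it from overlapping with the serious criteria. Say in the interview guide what the parent is being asked to report.

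Ask about it in the existing three-month parent interview, and report it to the monitoring committee as its own line. Base the by-arm summary on that interview, conducted by the blinded research assistant. List events reported spontaneously during the study separately, with a note that closer monitoring in the MATCH-ADTC arm may raise their number.

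The cost is one definition and one question in an interview already scheduled, plus somewhat more events to process. Parents will be recalling events three months after the post-intervention assessment, so some will be missed or misdated. Recruitment is under way, and about 50 participants had completed treatment by the blinded sample size review. Those past follow-up when the item is added will have no data on it, and the report should give the number asked in each arm. How such episodes are handled clinically is outside this point.

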### Changes to design during the trial

Two changes to the protocol were made during the course of the study.As recruitment was lower than planned, particularly for Māori and Pacific clinicians and participants, it became clear that we would not have sufficient numbers to allow for useful statistical analysis by ethnicity. As a consequence we have reduced the number of planned analyses by ethnicity and adjusted our sample size accordingly. More details are provided in the ‘Sample size’ section. However, we plan to augment the data we will have on the use of MATCH-ADTC for these two populations with a qualitative study of the acceptability of MATCH-ADTC to Māori and Pacific clinicians, participants, and their families.At the request of the Health Research Council’s independent data monitoring committee, who are overseeing the conduct and safety of the trial, we added to the data collection on serious adverse events by collecting information from parents at the three month follow-up interview on ‘moderate’ adverse events. More details on this are given below.

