### Outcome measures

The following outcome measures are collected during the trial. Most clinical measures are collected during the weekly telephone calls made by the research assistants according to the schedule of assessments listed in Table 1.

**Table 1 Tab1:** Summary schedule of data collected

Measure	Baseline	During therapy	After intervention	3-month follow-up	Informant	Collected by
Demographics	×				Child and parent	Clinician
Strengths and Difficulties Questionnaire	×	monthly	×	×	Child and parent	Research assistant
Brief Problem Monitor	×	weekly	×	×	Child and parent	Research assistant
Top Problems Assessment	×	weekly	×	×	Child and parent	Clinician at baseline and research assistant weekly
Development and Well-Being Assessment	×		×		Child (if 11 or over) and parent	Research assistant supports the family to complete online
Child Health Utility	×		×	×	Child	Research assistant
Medication use	×		×	×	Clinician and parent	Clinician at baseline and after intervention, research assistant at 3 months
Client satisfaction			×		Child and parent	Research assistant
Therapy Procedures Checklist			×		Clinician	Clinician
Serious adverse events		×			Clinician	Clinician
Moderate adverse events				×	Parent	Research assistant
Therapist Satisfaction Inventory			×		Clinician	Clinician
Recordings of therapy sessions		×			Clinician	Clinician
Therapy log			×		Clinician	Clinician

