### Blinding

Owing to the nature of the study, double blinding is not possible, as clinicians are aware of the treatment they are administering. We anticipate that despite signing informed consent, most youth and their parents will effectively be blind to treatment allocation. At entry to the study, the information conveyed to the participants (orally and in writing) has been designed to ensure that details that could easily distinguish MATCH-ADTC from usual care are not provided, but that accurate information is given. We explain that both treatments are thought to be effective and that the purpose of this research is to compare treatments to see if one is better than the other. All research assistants collecting telephone administered assessments and coding the therapy sessions are blind to treatment allocation throughout the study. Participants are asked not reveal the details of the intervention they are receiving to the research assistant. All participants are given an identification number to ensure that the researchers involved in data management and manipulation are unaware of the treatment allocation.

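### Serious adverse events have no described systematic capture after therapy ends, and the capture window, which follows therapy length, may differ between arms

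*Protocol article*

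**What the plan says.** Measures of harm defines a serious adverse event by four categories: death, suicide attempt, admission for non-suicidal self-harm, and admission for mental health problems. On who reports and when, it says "Clinicians are instructed to report serious adverse events at any stage during therapy within one working day of being aware of the event". In Table 1 (Outcome measures) the row reads "Serious adverse events × Clinician Clinician", and its single mark stands in the column for the therapy period. Nothing is marked after the intervention or at 3 months. The clinician is not blind; the Blinding section says that "double blinding is not possible, as clinicians are aware of the treatment they are administering".

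Moderate events are handled differently. Changes to design during the trial reports that, at the data monitoring committee's request, the team began "collecting information from parents at the three month follow-up interview on ‘moderate’ adverse events". Measures of harm adds: "Information on moderate adverse events is recorded when reported during the study and also collected from the parents at follow-up interview". The moderate list has three categories: "hospitalization for any medical reason, other than mental health problems", serious behavioral problems, and formal respite care.

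The number and types of serious and moderate events are a stated secondary outcome (Secondary outcomes), and both kinds of event go to the data monitoring committee.

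**The concern.** The four serious categories are among the most important harms for youths in mental health care, and they can occur after discharge or after a family stops attending. On the plan as described, those are the periods in which nobody is set to ask about them, although a blinded research assistant interviews the parent at the end of treatment and again three months later. That 3-month call asks about school suspension, for instance, but is not described as asking about a suicide attempt or a psychiatric admission.

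There is a second issue for the comparison between arms. If events count only while therapy lasts, each youth's observation window is the length of therapy. Overall analysis recognises that length may vary between the treatments and could not be matched, and chooses a trajectory-based primary outcome for that reason. The same reasoning is not carried over to serious events. If the arms did differ in duration, a raw comparison of counts would partly reflect exposure time, and the committee would see those counts.

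**Working it through.** No figure in the article bears directly on this point, so there is none to reproduce. The check is a comparison of sections, followed by an illustration on stated assumptions.

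**Sections side by side**

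- *Who and when.* Measures of harm and Table 1 agree: clinician, during therapy.
- *Does the parent interview fill the gap?* Its described content is the moderate list. Mental-health admission is expressly carved out; suicide attempt and death are not listed. A self-harm admission might surface if the parent regards it as medical.
- *Does recording of events reported during the study fill it?* That sentence concerns moderate events only.
- *Youths who leave therapy.* Withdrawal criteria keeps them in follow-up where possible, but no serious-event question is described for that follow-up.
- *Comparison within Table 1.* For medication use, collection passes from the clinician to the research assistant at 3 months. Serious events have no such handover.
- *Independent review.* The senior clinician outside the study reviews events already reported. This helps classification, not detection.

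**Illustration 1: share of on-study time without planned capture**

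Inputs: follow-up of three months after the post-intervention assessment (Three month follow-up), taken as 13 weeks; therapy length T in weeks, assumed because the article gives none; post-intervention assessment taken to fall at the end of therapy. Share = 13 / (T + 13).

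- T = 12: 13/25 = 52%
- T = 20: 13/33 = 39%
- T = 26: 13/39 = 33%
- T = 40: 13/53 = 25%

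**Illustration 2: effect of unequal windows when the true risk is the same**

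Assume a constant weekly hazard h, equal in both arms, of 0.001 or 0.002. Risk over a window T is 1 − exp(−hT). The apparent risk ratio is the ratio of the two risks.

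| Weeks, MATCH-ADTC v usual care (assumed) | Risks at h = 0.001 | Apparent ratio, therapy window | Apparent ratio, 13 weeks added to each arm |
|---|---|---|---|
| 20 v 20 | 1.98% v 1.98% | 1.00 | 1.00 |
| 16 v 20 | 1.59% v 1.98% | 0.80 | 0.88 |
| 20 v 26 | 1.98% v 2.57% | 0.77 | 0.85 |
| 20 v 30 | 1.98% v 2.96% | 0.67 | 0.77 |
| 30 v 20 | 2.96% v 1.98% | 1.49 | 1.30 |

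At h = 0.002 the therapy-window ratios are the same to two decimals; in the last column 20 v 30 becomes 0.78 and 30 v 20 becomes 1.29.

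Extending capture to 3 months closes the gap in coverage but only shrinks the window effect. Rates per person-time remove it under this model, because events divided by time at risk estimate h in each arm.

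**The case against.** The strongest reply is that several larger claims a reader might draw from these facts are not supported. This is largely right.

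- *That the arms have unequal windows, or that the protocol expects them to.* Overall analysis says only that durations may vary and could not be matched. The third primary hypothesis is equal or better efficiency, which is compatible with equal duration. With equal durations the apparent ratio is 1.00.
- *That later serious events are missed outright.* Some self-harm or overdose admissions to a medical ward could be reported under the moderate item. Cases may stay open for weeks after the planned last session (Discussion), and youths who leave therapy may still have a parent interview. The interview form is not shown. What is lacking is described, systematic prompting, not all contact.
- *That MATCH-ADTC clinicians detect more because only they see weekly progress data.* Those data are symptom and top-problem ratings; nothing says they reveal admissions or suicide attempts. A difference in detection is possible but speculative, and no direction can be assigned.
- *That any one pair of durations measures the bias.* The article gives no durations, event rates or drop-out by arm. The constant hazard is also an assumption: if events cluster soon after referral, both the loss and the distortion are smaller.

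It is also fair that serious events are one secondary outcome among many and that no primary conclusion rests on them. What remains is the ascertainment gap. Two places in the article fix clinician-only, therapy-only reporting, and no other text supplies a planned route afterwards. This is a stated design, not a detail left to a fuller document.

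**Conclusion.** The point holds in a limited form. As described, serious adverse events are collected only during therapy and only from the unblinded treating clinician. The 3-month parent interview, by its own definition, does not cover mental-health admissions and does not list suicide attempts. Events after discharge, or after a youth leaves therapy but remains in the study, are not systematically captured.

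On assumed therapy lengths of 12 to 40 weeks, the uncovered follow-up is about 52% to 25% of on-study time. For youths who leave therapy early and stay in the study, the uncovered part would be larger.

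Distortion between arms is conditional. It is absent if durations are equal, and reaches an apparent risk ratio of about 0.67 at 20 v 30 weeks with identical constant hazards. The coverage gap does not depend on durations differing. The change is worth making for the safety data; it does not bear on the primary analysis.

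**What to change.** Add the four serious-event items to the research assistant's existing post-intervention and 3-month parent interviews. Ask about the whole period since randomization, and include youths who left therapy but remain in the study. Report serious events by arm from randomization to the 3-month call, with person-time, showing clinician-reported and parent-reported events separately. Leave the clinicians' expedited reporting unchanged.

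The cost is a few questions in calls already made, plus an ethics notification. There are three downsides:

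- Youths already past their 3-month call will have clinician reports only. Reporting by source keeps this visible. Trial status says recruitment is still open, so an early change covers more of the sample.
- A parent describing an event may reveal the treatment to a blinded research assistant. Placing the items after the outcome measures protects that call's ratings.
- An event disclosed in a call must be passed into the existing serious-event reporting route, so the research assistants need an instruction to do so.
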